### 13.4 Reporting procedures for serious adverse events

As the infants involved in this study are premature, their underlying condition will lead to many adverse events which could be deemed 'Serious' due to meeting the criteria of:

- is life-threatening\*,

- requires hospitalisation or prolongation of existing hospitalisation,
- results in persistent or significant disability or incapacity,
- is a congenital anomaly or birth defect

For the purposes of this study, only events which meet the criteria below should be reported as Serious Adverse Events:

- results in death, or
- important medical events\*\*

\*Regarding a life-threatening event, this refers to an event in which the subject was at risk of death at the time of the event; it does not refer to an event which hypothetically might have caused death if it were more severe.

\*\*Some medical events may jeopardise the subject or may require an intervention to prevent one of the above characteristics/consequences. Such events (hereinafter referred to as 'important medical events') should also be considered as 'serious' in accordance with the definition.

The investigator will report all serious adverse events immediately to the sponsor except for those that the protocol or investigator's brochure identifies as not requiring immediate reporting. The immediate report will be followed by detailed, written reports. The immediate and follow-up reports will identify subjects by unique code numbers assigned to the latter.

The immediate report will be made by the investigator within a very short period of time and under no circumstances should this exceed **24 hours** following knowledge of the serious adverse event.

All SAE information must be recorded on an SAE forms and sent expeditiously to the sponsor to the specific pharmacovigilance team at the SAE reporting email address: [[contact]](mailto:[contact]) where they will be received and processed. Additional information received for a case (follow-up or corrections to the original case) need to be detailed on a new SAE form and sent expeditiously to the sponsor.

The sponsor will keep detailed records of all adverse events which are reported to him by the investigator or investigators.

In cases where reporting is not required immediately the investigator will report within the appropriate time frame, taking account of the specificities of the trial and of the serious adverse event, as well as possible guidance in the protocol or the Summary of product characteristics.

The sponsor will report all SUSARs to the competent authorities and the ethics committees concerned. Fatal or life-threatening SUSARs must be reported within **7 days**. SUSARs which are not fatal and not life-threatening are to be reported within **15 days**. The sponsor will also inform all investigators concerned of relevant information about SUSARs that could adversely affect the safety of subjects. If the initial report is incomplete, e.g. if the sponsor has not provided all the information/assessment within seven days, the sponsor will submit a completed report based on the initial information within an additional eight days.

If significant new information on an already reported case is received by the sponsor, the clock starts again at day zero, i.e. the date of receipt of new information. This information will be reported as a follow-up report within **15 days**.

In addition to the expedited reporting above, the sponsor shall submit once a year throughout the clinical trial or on request, a safety report to the competent authority and ethics committees. The annual safety report will be presented in the DSUR format as per ICH guideline E2F - Note for guidance on development safety update reports. This is a legal requirement.

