## 13.3 Reporting procedures for all adverse events

The investigational medicinal product (IMP), Curosurf, is licensed for use for prevention and treatment of respiratory distress syndrome (RDS) in premature infants in Europe for more than 25 years. It is given as a single dose by the endotracheal route and may on occasion be repeated. It has an excellent safety profile.

Many of the adverse events which are listed in the Summary of Product Characteristics for Curosurf (portactant alfa) below occur commonly in preterm infants who are admitted to the Neonatal Intensive Care Unit (NICU), whether or not they have received surfactant. Others are seen infrequently in this population, whether or not they have received surfactant.

| System organ Class                              | Adverse Reaction                     | Frequency |
|-------------------------------------------------|--------------------------------------|-----------|
| Infections and infestations                     | Sepsis                               | Uncommon  |
| Nervous system disorders                        | Haemorrhage intracranial             | Uncommon  |
| Cardiac disorders                               | Bradycardia                          | Rare      |
| Vascular disorders                              | Hypotension                          | Rare      |
| Respiratory, thoracic and mediastinal disorders | Bronchopulmonary dysplasia           | Rare      |
|                                                 | Pneumothorax                         | Uncommon  |
|                                                 | Pulmonary haemorrhage                | Rare      |
|                                                 | Hyperoxia                            | Not known |
|                                                 | Cyanosis neonatal                    | Not known |
| Investigations                                  | Apnoea                               | Not known |
|                                                 | Oxygen saturation decreased          | Rare      |
|                                                 | Electroencephalogram abnormal        | Not known |
| Injury, poisoning and procedural complications  | Endotracheal intubation complication | Not known |

AEs that are directly related to the underlying condition of extreme prematurity do not need to be reported as an AE on this study, for example:

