1. Bradycardia, hypotension, hyperoxia, cyanosis, apnoea, oxygen desaturations  
These events frequently occur several times per day in this population, whether or not they have received surfactant. Most often these events are short in duration and not of clinical significance. Regular reporting of these adverse events in the CRF is not required.
2. Intracranial haemorrhage  
Some degree of intracranial haemorrhage is detected in  $\geq 30\%$  of infants in this population, whether or not they have received surfactant. Regular reporting of these adverse events in the CRF is not required. All enrolled infants are being screened for intracranial haemorrhage; it is being recorded in the CRF and measured as a secondary outcome.
3. Bronchopulmonary dysplasia  
Bronchopulmonary dysplasia occurs in up to  $\geq 50\%$  in this population of infants, whether or not they have received surfactant. Regular reporting of these adverse events in the CRF is not required. All enrolled infants are being screened for bronchopulmonary dysplasia; it is being recorded in the CRF and measured as a secondary outcome.
4. Pneumothorax, pulmonary haemorrhage  
These are rare events in this population of infants, whether or not they have received surfactant. Regular reporting of these adverse events in the CRF is not required. All enrolled infants are being screened for pneumothorax and pulmonary haemorrhage; it is being recorded in the CRF and measured as a secondary outcome.
5. Endotracheal intubation complication  
Endotracheal intubation complication is not relevant as we are not giving surfactant via this route of administration as the intervention arm for this study. Regular reporting of these adverse events in the CRF is not required.

Only AEs which are not directly associated to the underlying condition of extreme prematurity should be reported. The following information will be recorded: description, date of onset and end date, severity, assessment of relatedness to the study medication, other suspect medication or device and action taken. Follow-up information should be provided as necessary.

AEs considered related to the study medication as judged by an investigator or the sponsor will be followed until resolution or until the event is considered stable. All related AEs that result in a subject's withdrawal from the study or are present at the end of the study, should be followed up until a satisfactory resolution occurs.

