#### **14.6 Safety analysis**

Adverse events following administration of oropharyngeal surfactant will be documented e.g. bradycardia, desaturation. Should an infant require endotracheal intubation for respiratory failure, the intubation difficulty and attempts after oropharyngeal administration of surfactant will also be recorded.

Safety analyses will be carried out on patients in the Safety Set, the definition of which will be finalized in the Statistical Analysis Plan (SAP).

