### 4.4 Baseline patient characteristics

Evaluations of the baseline characteristics will be based on the FAS. They will be presented in a descriptive summary table by treatment group—continuous variables as mean and standard deviation or median and quartiles, and categorical variables as absolute and relative frequencies. No statistical comparisons of patient characteristics at baseline will be performed.

Maternal baseline characteristics to be summarized include

- Age
- Ethnicity
- In Utero antenatal transfer
- Administration of antenatal steroids (incidence and number of doses)
- Spontaneous labour
- Preterm premature rupture of membranes (evidence of and duration of),
- Intra-partum antibiotic use
- Mode of delivery and
- Indication for mode of delivery
- Administration of regional anaesthesia (e.g. spinal, epidural)
- Administration of general anaesthesia

Infant baseline characteristics to be summarized include

- Best estimate of gestational age (GA)
- Method for determining GA
- Gender
- Multiplicity
- Birth weight

|         |                                           |               |
|---------|-------------------------------------------|---------------|
| UCD CRC | SAP for the POPART trial                  |               |
| UCD CRC | Template: Statistical Analysis Plan (SAP) | Version: 1.0  |
|         |                                           | Page 11 of 19 |

- Apgar scores (1, 5, 10 min)
- resuscitation at delivery

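### Sections 13.3 and 13.4 leave the capture of acute events after the bolus to investigator judgement, in conflict with 14.6, 13.1.3 and the SUSAR timeline, and SAP 4.4 labels post-randomisation delivery-room measures as baseline

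*Combined protocol and SAP*

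**What the plan says.** **Non-serious events.** Protocol 13.3 states that "AEs that are directly related to the underlying condition of extreme prematurity do not need to be reported as an AE on this study". The first group of examples is "Bradycardia, hypotension, hyperoxia, cyanosis, apnoea, oxygen desaturations", justified as frequent, brief and usually unimportant in this population. For this group, as for the others, "Regular reporting of these adverse events in the CRF is not required". The section then adds: "Only AEs which are not directly associated to the underlying condition of extreme prematurity should be reported".

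**Safety analysis.** Protocol 14.6 states: "Adverse events following administration of oropharyngeal surfactant will be documented e.g. bradycardia, desaturation". Sections 9.2 and 11.3.2 both name bradycardia and desaturation as known effects of the product.

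**Serious events.** Protocol 13.1.3 lists six criteria, and 13.2.1 tells investigators to assess seriousness by the definitions in 13.1. Section 13.4 states: "For the purposes of this study, only events which meet the criteria below should be reported as Serious Adverse Events", and names death and important medical events. Later in 13.4, "Fatal or life-threatening SUSARs must be reported within" seven days.

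**Baseline.** SAP 4.4 lists Apgar scores at 1, 5 and 10 minutes and resuscitation at delivery among infant baseline characteristics, tabulated by treatment group, and says: "No statistical comparisons of patient characteristics at baseline will be performed". Protocol 14.4 also places these measures with the baseline data.

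**The concern.** The trial gives a licensed product by an unlicensed route, as a bolus into the oropharynx within minutes of birth. The effects the protocol itself expects are acute ones: slowing of the heart and loss of oxygenation. Those are the events that 13.3 puts on its exempt list. The reason given there describes background events over a NICU stay, not the first minutes after a bolus.

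A site that follows 13.3 gives the analysis in 14.6 no assured data. A site that follows 14.6 collects data that 13.3 says it need not collect. Staff know the allocation, so whatever is left to judgement may be reported differently in the two arms. Section 13.4 matters for monitoring as well, because the DSMB's safety trigger in 13.5 is an excess of serious adverse events in the intervention group.

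**Working it through.** The point rests on text, so the check sets the sections side by side.

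**1. Do the exempted events have another route into the data?** Section 13.3 exempts five groups. Compare each with the secondary outcomes in protocol 10.3 and SAP 1.3:

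| Exempted in 13.3 | Captured elsewhere? |
|---|---|
| Bradycardia, hypotension, hyperoxia, cyanosis, apnoea, desaturation | No secondary outcome; 14.6 says bradycardia and desaturation will be documented |
| Intracranial haemorrhage | Yes: any and severe IVH |
| Bronchopulmonary dysplasia | Yes: oxygen at 28 days |
| Pneumothorax, pulmonary haemorrhage | Yes: both |
| Intubation complication | In part: number of attempts in the delivery room |

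Only the first group has no backup outcome. SAP 5.4 gives it no analysis of its own, so it depends on what is reported as an AE. Vital signs are recorded on the day of birth (11.3.1, 11.3.4), but the listed signs do not include oxygen saturation and are not tied to the time of the dose.

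**2. Is there an exception for suspected drug effects?** Section 13.3 states none, by timing or by causality. Relatedness is recorded for events that pass the prematurity filter. The sentence in 13.3 on AEs considered related concerns their follow-up, not whether they are first reported. The word regular is not defined.

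**3. Seriousness criteria.** 13.1.3 lists six: death, life-threatening, hospitalisation or its prolongation, disability, congenital anomaly and important medical event. 13.4 keeps two, so 6 − 2 = 4 are removed as stand-alone triggers, in both arms and whatever the suspected cause. One of the four, life-threatening, is the criterion on which the seven-day SUSAR timeline depends.

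**4. Timing of the measures called baseline.** The envelope is opened immediately before birth (11.3.6) and the dose is given within 5 minutes of birth (11.1). All Apgar scores therefore follow randomisation. The 1-minute score may fall before or after the dose. The 10-minute score comes at least 10 − 5 = 5 minutes after every dose given per protocol.

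**5. What the DSMB sees.** Section 13.5 gives it AE frequency and severity by arm every six months, and the primary outcome and death at 126 infants. The protocol does not say that it receives the delivery-room secondary outcomes.

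**The case against.** The strongest reply is that the plan can be read sensibly. Several parts of that reply stand.

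- A reader might infer that post-bolus events are expressly exempt. The documents do not say so. The exemption covers events directly related to prematurity and waives regular reporting, and 13.2.2 treats any possibly or probably related event as an adverse reaction. An investigator could report a suspected bolus reaction. But nothing in 13.3 makes that clear, and 14.6 needs the data whatever the investigator's view.
- A reader might infer that life-threatening events are exempt outright. They are not. The retained important-medical-event criterion covers events that may endanger the infant or need intervention to avert a listed consequence. The mismatch with the SUSAR timeline is therefore a gap filled by judgement, not a flat contradiction. Bradycardia and desaturation are also listed in the product information used for expectedness, so they would be SUSARs only if their nature or severity departed from it.
- A reader might infer that all early resuscitation data are hidden in the baseline table. They are not. Delivery-room intubation, chest compressions and adrenaline are secondary outcomes compared by arm. The concern is confined to Apgar scores and the remaining resuscitation measures, and even these are tabulated by arm.
- The Document History entry for version 2.1 says close-out had begun at certain sites, and the SAP is dated 27/04/22. New CRF items cannot be collected prospectively for infants at closed sites.

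**Conclusion.** The point holds in a limited form. Sections 13.3 and 14.6 disagree on whether bradycardia and desaturation after the bolus are recorded, and these events have no backup outcome. Section 13.4 drops the stand-alone life-threatening criterion that 13.1.3 defines and the SUSAR timeline uses. SAP 4.4 treats post-randomisation measures as baseline.

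It would go too far to say that the DSMB is blinded to acute harm. It still reviews deaths, important medical events and reported AEs by arm, and the delivery-room secondary outcomes are compared in the final analysis. What is weakened is its view of non-fatal acute events, which depends on open-label judgement.

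The size cannot be given as a number, because the documents state no rate for these events. In the text, both reactions named in 14.6 are on the exempt list, and four of six seriousness criteria no longer trigger a report by themselves. Sample size, power and type I error are not affected. The conclusion assumes that sites apply 13.3 and 13.4 as written and that no CRF instruction outside these documents resolves the conflict.

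**What to change.** 1. In 13.3 and 13.4, limit the exemptions to events judged unrelated to study treatment. Report any event suspected to be related under all six criteria in 13.1.3. This reconciles 13.3 with 14.6, and 13.4 with 13.1.3 and the SUSAR timeline.
2. Record bradycardia, desaturation and apnoea from birth to NICU admission as yes/no CRF items in both arms, as 14.6 implies. State in 13.5 which acute-event data the DSMB receives.
3. In SAP 4.4, move the Apgar scores and the resuscitation measures not already secondary outcomes out of the baseline table. Report them by arm as post-randomisation outcomes with 95% confidence intervals, and align protocol 14.4.

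The cost is protocol and SAP wording, a few CRF items and some extra SAE forms. Where sites have closed, item 2 can only be done from source records where available, and the report should state the limitation. Item 3 needs only an SAP change where the data are already on the CRF.

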### 13.5 Data Safety Monitoring Board (DSMB)

A DSMB will be established to perform ongoing safety surveillance and to perform interim analyses on the study data. The DSMB will be an independent committee, composed of a minimum of three members; at least two will be clinicians not involved in the trial but with experience and expertise in clinical trials; at least one member will be a clinician with expertise in neonatology. Each member will state that they have no conflict of interest with the sponsor or company involved in the study or any other conflicting interest to declare.

The DSMB will meet on a 6-monthly basis after start of the trial and will review the frequency and severity of adverse events in both treatment groups. If they observe any significant excess of serious adverse events in the intervention group associated with the intervention, they may recommend premature termination of the trial on the basis of serious safety concerns.

The DSMB will also conduct interim analysis to determine whether the data provide overwhelming evidence of efficacy or futility, defined as a highly statistically significant difference (i.e.  $P < 0.001$ ) in the primary outcome or a highly statistically significant difference in the important secondary outcome of death before hospital discharge. Interim analysis for efficacy or futility will be carried out after approximately 50% of participants ( $n=126$ ) have completed the study. The DSMB may recommend early termination of the trial due to efficacy or futility.

The advice(s) of the DSMB will be notified upon receipt by the sponsor to the REC and CA that approved the protocol. With this notification a statement will be included indicating whether the advice will be followed.

## 14 STATISTICS

### 14.1 Description of statistical methods

A Statistical Analysis Plan (SAP) will be written by the trial statistician. The SAP will detail the implementation of all of the planned statistical analysis in accordance with the main features stated in this section of the protocol and amendments if applicable. The SAP must be finalized before the database is locked, which is required to commence the study analysis.

### 14.2 Determination of sample size subjects

In randomised studies, the rate of mechanical ventilation in the days after birth among preterm infants treated with CPAP alone has varied from 46– 60%. (2, 11, 19-21) Minimally invasive surfactant techniques were shown to reduce the rate of mechanical ventilation to from 46% to 28% in a cohort of infants with a gestational age between 26 and 28 weeks. (21)

Sample size for this study was calculated in G\*power, using a two-sided, two-proportion Z test. To detect a difference in the rate of endotracheal intubation for respiratory failure of 18% between treatment arms (assuming a rate of 46% in the control group and 28% in the intervention arm) with 80% power and a 5% significance level, a sample size of 224 infants would be required. To compensate for a death rate of 10% (estimated from local data, The National Maternity Hospital, Neonatal Clinical Report for 2015) before the primary outcome can be determined (i.e. at 120 hours), we will need to recruit a total of **250** infants to this study.

The National Maternity Hospital is a stand-alone university maternity hospital with a tertiary NICU to which > 150 infants < 1500g are admitted annually. We have a track record of initiating, conducting, completing, presenting and publishing investigator-led randomised controlled trials, including trials that compared delivery room interventions, (12-14) trials that had respiratory failure in the NICU as the primary outcome (15) and trials that compared investigational medicinal products (16) in preterm infants. Though the enrolment rates to our studies amongst eligible infants are consistently excellent (> 80%), we believe it will be necessary to enrol infants at multiple sites in order to enrol our planned target sample of 250 infants in a timely fashion. We have a track record enlisting the help of collaborators

nationally(16)andinternationally(14, 17)to perform our studies. We believe that with their help, we can enrol these infants in 2–3 years.

### 14.3 Analysis sets

This table defines the sets of subjects whose data are to be included in the statistical analyses.

|                                                     |                                                                                                                                                                                                                                                                                                                                                                        |
|-----------------------------------------------------|------------------------------------------------------------------------------------------------------------------------------------------------------------------------------------------------------------------------------------------------------------------------------------------------------------------------------------------------------------------------|
| Full Analysis Set
(Intention-To-Treat principle) | All randomized patients                                                                                                                                                                                                                                                                                                                                                |
| Per Protocol Set                                    | Patients in the Full Analysis Set, excluding those with relevant protocol deviations which could affect the evaluation of primary endpoint. The Per Protocol set will exclude: 
 
• Infants in the intervention arm who did not receive study treatment
 
• Infants with incomplete data on the primary endpoint
 
 |
| Safety Set                                          | Patients in the intervention arm who received prophylactic surfactant and all patients in the control arm (for comparison)                                                                                                                                                                                                                                             |

Efficacy analysis will be carried out following the Intention-To-Treat (ITT) principle. Per protocol analysis of the primary endpoint will also be carried out for sensitivity analysis. Safety data will be analysed using the safety set.

